### Study Population

Patients with perianal abscesses who have surgical indications and meet the inclusion criteria are being recruited from the Anorectal Department of the Shanghai Hospital of Traditional Chinese Medicine between April 2025 and October 2026.

The diagnostic criteria are formulated with reference to the diagnostic part of perianorectal abscess in Chinese Anorectal Diseases [18] and the diagnostic part of perianorectal abscess issued by the State Administration of Traditional Chinese Medicine in 2012 [19]. The systemic symptoms may include chills, high fever, general weakness, and lack of appetite. Additionally, the patient may experience anal swelling, difficulty, or pain when defecating. The presence of hard nodules or lumps around the anal canal, localized pressure or fluctuating sensation, and increased skin temperature. Palpation of the affected area reveals a slightly hard or fluctuating soft mass and a worsening of the pain when pressure is applied. Congested and swollen anal sinus with purulent secretion upon pressing. A puncture examination is conducted, whereby pus is successfully extracted from the most prominent swelling and congestion of the rectal mucosa observed under an anoscope. This procedure proves invaluable in facilitating an accurate diagnosis. A blood routine examination reveals an increase in the total number of white blood cells and neutrophils.

The inclusion criteria are as follows: (1) informed consent and signed informed consent form; (2) meeting the diagnostic criteria of perianal abscess according to both Western medicine and traditional Chinese medicine syndrome of heat and toxin; (3) aged 15 to 80 years; (4) willing to participate and cooperate in completing the required surgical treatment; (5) agree to participate in this experimental study without accepting any other treatment options. In contrast, the exclusion criteria are as follows: (1) patients younger than 15 years old or older than 80 years old; (2) patients who refuse to participate in the study; (3) patients with severe primary diseases of the liver, kidney, hematopoietic system, endocrine system, cardiovascular and cerebrovascular system, nervous system, tuberculosis, vertebral malformation, malignant tumors, or mental illness; (4) patients with a suspected history of abuse of sedative-hypnotics, opioid analgesics, or alcohol. Patients with skin diseases or infectious diseases; (5) individuals with metal implants who cannot undergo MRI; (6) pregnant women, women preparing to become pregnant, or lactating women; (7) individuals who are not suitable or unable to use this treatment for other reasons; (8) individuals with mental disorders, language disorders, motor dysfunction, or psychological diseases.

### Ethical Considerations

The trial is being conducted in accordance with the ethical standards of the Declaration of Helsinki. Ethical approval has been obtained from the Ethics Committee of Shanghai Municipal Hospital of Traditional Chinese Medicine (2023SHL-KYYS-104). Written informed consent is being obtained from all participants after a detailed explanation of the study objectives, procedures, potential risks, and rights (including the right to withdraw at any time without prejudice to clinical treatment), ensuring full comprehension before enrollment. To protect participant privacy and confidentiality, all collected data are being deidentified immediately after acquisition (personal identifiers are replaced with unique study serial numbers) and stored in password-protected electronic databases or locked file cabinets with access restricted to authorized personnel only. No financial compensation is provided to participants for participation in this trial.

### Treatment Plan

Both groups undergo an identical perianal MRI protocol on the same 3.0-T scanner using a 16-channel abdominal phased-array coil, with all participants scanned in the supine position. The sole distinction between the 2 imaging protocols lies in the diffusion-weighted sequence: the control group receives conventional DWI, whereas the intervention group undergoes DTI. Crucially, both groups receive intravenous gadolinium-based contrast agent (GD-DTPA) and subsequent identical postcontrast sequences. All remaining sequences, including T1-weighted, T2-weighted, and fat-suppressed T2-weighted imaging, are standardized across groups.

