### Conventional MRI Group

The conventional MRI group underwent imaging using a 3.0-T Philips Ingenia magnetic resonance system equipped with a 16-channel abdominal phased-array coil, with patients scanned in the supine position. The scanning protocol includes the following sequences and parameters. Sagittal fast spin-echo T2-weighted imaging (FSE T2WI) is acquired with an echo time (TE) of 85 ms, repetition time (TR) of 4000 ms, slice thickness of 3.5 mm, slice spacing of 0.5 mm, and matrix size of 416 × 224. Oblique axial FSE T2WI and oblique axial fat-suppressed T2WI are obtained using identical parameters: TE 85 ms, TR 4000 ms, slice thickness 3.5 mm, slice spacing 0.5 mm, and matrix 416 × 224. DWI is performed in the oblique axial plane with a TE of 71 ms, TR of 2000 ms, slice thickness of 5 mm, slice spacing of 1 mm, and a b-value of 800 s/mm². For T1-weighted imaging (T1WI), oblique axial FSE T1WI is acquired with minimum TE, a TR of 400 ms, slice thickness of 3.5 mm, slice spacing of 0.5 mm, and matrix size of 416 × 224. Following intravenous administration of gadolinium-based contrast agent (GD-DTPA), spoiled gradient–recalled echo sequences are performed in oblique axial, oblique coronal, and sagittal orientations, with minimum TE, TR of 200 ms, flip angle of 70°, slice thickness of 3.5 mm, slice spacing of 0.5 mm, and matrix dimensions of 320 × 256.

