### The DTI Group

The DTI group is scanned using a 3.0-T Philips Ingenia magnetic resonance imager with a 16-channel abdominal phased array coil, with all participants positioned supine during imaging. The scanning protocol comprises several sequences conducted with specific parameters. Turbo spin-echo T1WI is performed with a TR of 600 ms, TE of 10 ms, a slice thickness of 5 mm, and a total of 20 slices. For transverse axial imaging, both turbo spin-echo T2-weighted and fat-suppressed T2-weighted sequences are acquired using a TR of 1560 ms, TE of 80 ms, slice thickness of 5 mm, and 20 slices. Sagittal fat-suppressed T2WI is carried out with a field of view of 152 × 179 mm, slice thickness of 5 mm, and 20 slices. DTI is conducted using a spin-echo echo-planar imaging sequence with a single excitation in the transverse axis, employing a TR of 3250 ms, TE of 48 ms, 32 diffusion directions, b values of 0 and 600 s/mm², slice thickness of 5 mm, 20 slices, and a total scan time of 5 minutes and 47 seconds.

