## Discussion

This study is designed to test the hypothesis that preoperative DTI, compared with conventional MRI, can provide superior visualization of perianal abscess extent and muscular involvement, thereby guiding more precise surgical excision and leading to a lower 6-month recurrence rate.

Currently, there is only 1 comparative study between DTI and MRI for perianal fistula [16], and no specific studies have been reported on the location depth, size, thickness of anal canal and rectum, and thickness of the levator ani muscle and internal and external sphincter of perianal abscesses. This protocol builds upon the feasibility shown in fistula imaging but shifts the focus to preoperative mapping of abscess morphology and infiltration—a critical gap in current clinical practice.

Perianal abscess is a common disease in the anorectal department, and surgery remains the most effective and complete cure treatment [22]. However, the relationship between the extent of abscess involvement and surrounding inflammatory infiltration is not determined before the operation, which can increase the risk of postoperative recurrence [23]. Although conventional MRI sequences have some diagnostic value in determining the extent of disease, they have limitations in distinguishing abscesses from inflammatory masses [24,25]. Therefore, a contrast agent that shows the characteristic edge enhancement of an abscess is often used in combination. However, there are increasing concerns regarding contrast injection, especially in patients with renal insufficiency, and the association between contrast exposure and nephrogenic systemic fibrosis has been emphasized [26]. Therefore, the search for alternative imaging techniques that do not use contrast agents has been an important topic, especially for high-risk patients, while ensuring that diagnostic value is maintained. DTI can clearly show the degree of infection infiltration, the extent of the abscess, and the relationship between the erosion of tissue and muscle around the pelvic floor [27,28]. This makes DTI essential for reducing the chance of recurrence. In addition, the fractional anisotropy and apparent diffusion coefficient values of the DTI parameters may play a role in assessing the extent and activity of the perianal abscess.

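### The Treatment Plan says the arms differ only in the diffusion sequence, but the two listed scan protocols also differ in T1, axial T2 and sagittal T2; if patients are scanned as listed, a difference in recurrence cannot be credited to DTI versus DWI

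*Protocol article*

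**What the plan says.** The Treatment Plan section of the protocol article makes four statements about the arms:

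- "Both groups undergo an identical perianal MRI protocol on the same 3.0-T scanner"
- "The sole distinction between the 2 imaging protocols lies in the diffusion-weighted sequence" (DWI in the control group, DTI in the intervention group)
- On the anatomical imaging: "All remaining sequences, including T1-weighted, T2-weighted, and fat-suppressed T2-weighted imaging, are standardized across groups"
- On contrast: "both groups receive intravenous gadolinium-based contrast agent (GD-DTPA) and subsequent identical postcontrast sequences"

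The next two sections give scan parameters arm by arm. For oblique axial T2 and fat-suppressed T2 in the Conventional MRI Group section, the values are "TE 85 ms, TR 4000 ms, slice thickness 3.5 mm, slice spacing 0.5 mm, and matrix 416 × 224". In The DTI Group section, the transverse axial T2 and "fat-suppressed T2-weighted sequences are acquired using a TR of 1560 ms, TE of 80 ms, slice thickness of 5 mm". The conventional list ends with contrast injection and spoiled gradient-recalled echo imaging in three orientations. The DTI list ends with the DTI sequence and does not mention contrast.

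Under Randomization, the surgeon reads the imaging report produced under the assigned protocol before operating and bases the surgical plan on it. The primary outcome is recurrence at 6 months.

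**The concern.** The imaging protocol is the randomised intervention, and its route to the primary outcome is the surgical plan built on the imaging report. Anything in the scan that differs by arm can travel that same route. Randomisation does not balance it out, because it is part of what is assigned. The claim that only the diffusion sequence differs is what would allow a difference in recurrence to be credited to DTI rather than DWI. If slice thickness, plane, fat suppression or repetition time also differ by arm, that attribution is lost.

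The structured report is exposed as well. It covers abscess location, extent and thickness and the relation to muscle, it draws on the preoperative images, and its items are compared between groups.

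**Working it through.** The article states no figure that could be reproduced for this point. The check sets the two parameter lists side by side against the claim that everything except diffusion is standardised. The diffusion rows are left out because they are the declared difference.

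| Component | Conventional MRI Group section | The DTI Group section | Conflict shown? |
|---|---|---|---|
| Scanner, coil, position | 3.0-T, 16-channel, supine | same | No |
| T1 | oblique axial, TR 400 ms, minimum TE, 3.5 mm | TR 600 ms, TE 10 ms, 5 mm | Yes: TR and thickness |
| Axial T2 | oblique axial, TR 4000 / TE 85 ms, 3.5 mm | transverse axial, TR 1560 / TE 80 ms, 5 mm | Yes: plane, TR, TE, thickness |
| Axial fat-suppressed T2 | as axial T2 | as axial T2 | Yes: same items |
| Sagittal T2 | fat suppression not stated, 3.5 mm | fat-suppressed, 5 mm | Yes: thickness; fat suppression as listed |
| Postcontrast | 3 orientations | none listed | Silence, not a contrary statement |

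**Count.** Four non-diffusion, non-contrast sequences appear in both lists (T1, axial T2, axial fat-suppressed T2, sagittal T2). All four differ in at least one stated value.

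**Slice thickness.** In all four it is 3.5 mm against 5 mm. 5 / 3.5 = 1.43, so slices are listed as 43% thicker in the DTI arm. This describes the scans; nothing in the document converts it into an effect on recurrence.

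**What cannot be compared.** The T1 echo time is given as minimum in one list and 10 ms in the other; without the minimum value no difference is shown. Slice spacing is 0.5 mm in the conventional arm and not stated in the DTI arm, so the distance between slice centres cannot be compared.

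**Could an analysis by scan version rescue attribution later?** Inputs: 37 enrolled by January 2026 (Results), and assumed recurrence of 15% and 5% (Sample Size Calculation). With an even split, 37 / 2 = 18.5 per arm. Expected events among these patients: 18.5 × 0.15 + 18.5 × 0.05 = 2.8 + 0.9 = 3.7, or about 4. A between-arm comparison on about 4 events says very little. Scan version would also coincide with calendar time.

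**The case against.** The strongest reply is that the Treatment Plan section is explicit and was evidently written to settle this very question, so the parameter lists may simply be wrong. In that case the non-diffusion imaging does not differ and the error is one of documentation. That possibility stands, and it is why the consequence is stated conditionally. It does not remove the contradiction. Both lists give positive values for TR, TE, plane and thickness; neither condensation into an article nor a broken table turns one set into the other.

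Three stronger readings are tempting, and the document does not support them.

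- *The DTI arm is scanned without contrast.* A reader might infer this from the DTI list. But that list is only silent, and the Treatment Plan section expressly gives contrast and the same postcontrast sequences to both groups. An incomplete list is a natural explanation.
- *The Discussion confirms a contrast-free DTI arm.* A reader might take the remark that "the search for alternative imaging techniques that do not use contrast agents has been an important topic" that way. It is general background with high-risk patients in view. It says nothing about how this trial's DTI arm is scanned and is compatible with contrast in both arms.
- *The trial is invalid, or DTI is certainly confounded.* Even if the arms are scanned as listed, randomisation still gives a fair comparison of two imaging packages. The Study Design section itself frames the comparison as DTI group against conventional MRI group; it is the Treatment Plan section that narrows it to the diffusion sequence. Only the narrower attribution would be lost.

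**Conclusion.** The point holds as an unreconciled contradiction with a conditional consequence. The statement that only diffusion differs cannot be true together with both parameter lists: all four shared non-diffusion sequences conflict in at least one value, each with 3.5 against 5 mm slices. The postcontrast sequences are promised to both arms but listed for one, which may be an omission.

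If patients are scanned as the two lists say, a difference in recurrence compares one imaging package with another and cannot be credited to DTI over DWI. The direction and size of any contribution from the other sequences cannot be derived from the document. If the Treatment Plan section describes what is done, there is no such problem of attribution and the lists need correcting. The document alone cannot decide between the two, but the scan headers can. Either way a reader cannot at present tell which intervention was tested.

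**What to change.** 1. Check the scan headers of all patients already enrolled (37 by January 2026) and record which sequences and parameters were acquired in each arm, postcontrast imaging included. Do this first, so that the rewriting does not presume which section is right.
2. Reconcile the three sections in one sequence table covering both arms, with a row for postcontrast imaging. The radiology lead decides the parameters.
3. If the headers show the same non-diffusion sequences in both arms, correct the parameter lists. Nothing else changes.
4. If they show that the arms differed, align the non-diffusion sequences for the remaining patients through an amendment. Report how many patients in each arm were scanned under each version, and word the conclusion as DTI protocol package versus conventional MRI protocol package. Any analysis by scan version should be descriptive only.

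Cost: a header check and a rewritten section in every case. If the arms differed, add a change to the scanner preset, together with the Ethics Committee approval before implementation and the registry update that the Management of Protocol Amendments section requires. No extra patients are needed. Recruitment is planned to October 2026, so the sooner the check is made, the more patients a correction can cover.

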### Conventional MRI Group

The conventional MRI group underwent imaging using a 3.0-T Philips Ingenia magnetic resonance system equipped with a 16-channel abdominal phased-array coil, with patients scanned in the supine position. The scanning protocol includes the following sequences and parameters. Sagittal fast spin-echo T2-weighted imaging (FSE T2WI) is acquired with an echo time (TE) of 85 ms, repetition time (TR) of 4000 ms, slice thickness of 3.5 mm, slice spacing of 0.5 mm, and matrix size of 416 × 224. Oblique axial FSE T2WI and oblique axial fat-suppressed T2WI are obtained using identical parameters: TE 85 ms, TR 4000 ms, slice thickness 3.5 mm, slice spacing 0.5 mm, and matrix 416 × 224. DWI is performed in the oblique axial plane with a TE of 71 ms, TR of 2000 ms, slice thickness of 5 mm, slice spacing of 1 mm, and a b-value of 800 s/mm². For T1-weighted imaging (T1WI), oblique axial FSE T1WI is acquired with minimum TE, a TR of 400 ms, slice thickness of 3.5 mm, slice spacing of 0.5 mm, and matrix size of 416 × 224. Following intravenous administration of gadolinium-based contrast agent (GD-DTPA), spoiled gradient–recalled echo sequences are performed in oblique axial, oblique coronal, and sagittal orientations, with minimum TE, TR of 200 ms, flip angle of 70°, slice thickness of 3.5 mm, slice spacing of 0.5 mm, and matrix dimensions of 320 × 256.

### The DTI Group

The DTI group is scanned using a 3.0-T Philips Ingenia magnetic resonance imager with a 16-channel abdominal phased array coil, with all participants positioned supine during imaging. The scanning protocol comprises several sequences conducted with specific parameters. Turbo spin-echo T1WI is performed with a TR of 600 ms, TE of 10 ms, a slice thickness of 5 mm, and a total of 20 slices. For transverse axial imaging, both turbo spin-echo T2-weighted and fat-suppressed T2-weighted sequences are acquired using a TR of 1560 ms, TE of 80 ms, slice thickness of 5 mm, and 20 slices. Sagittal fat-suppressed T2WI is carried out with a field of view of 152 × 179 mm, slice thickness of 5 mm, and 20 slices. DTI is conducted using a spin-echo echo-planar imaging sequence with a single excitation in the transverse axis, employing a TR of 3250 ms, TE of 48 ms, 32 diffusion directions, b values of 0 and 600 s/mm², slice thickness of 5 mm, 20 slices, and a total scan time of 5 minutes and 47 seconds.

### Perioperative Management

All surgical procedures in this trial are being performed by surgeons who hold senior professional titles and possess extensive surgical experience. Prior to surgery, preoperative communication is conducted between the medical team and each patient to ensure a clear understanding of the procedural steps and to facilitate cooperation during treatment. Preoperative preparations include an 8-hour fasting and 6-hour fluid restriction period before the procedure. Patients are instructed to take laxatives on the evening prior to surgery and to undergo a cleansing enema on the morning of the operation.

On the day of surgery, perianal hair is shaved and the local area is thoroughly cleansed. Patient positioning—whether lithotomy, prone jackknife, or lateral decubitus—is determined based on the specific location and characteristics of the abscess. Intravenous anesthesia is administered routinely, with general anesthesia reserved for special clinical circumstances.

The surgical approach is decided following a comprehensive evaluation that incorporates the patient’s clinical symptoms, findings from specialized physical examination, and results from auxiliary imaging. The selected intervention is a one-time radical resection of the perianal abscess, aiming to completely address the primary lesion and achieve a curative outcome.

Postoperative care begins on the first day after surgery, with wound dressings being changed twice daily at 8:00 AM and 6:00 PM. During each dressing change, iodophor-soaked cotton balls are used to gently cleanse the pus cavity, wound surface, and any necrotic tissue surrounding the drainage line or tube. Additional wound management interventions, such as cavity irrigation, negative pressure suction, or pad compression, are applied as clinically indicated. In cases where postoperative blood tests suggest infection, intravenous administration of cefuroxime sodium combined with metronidazole is initiated as anti-infective therapy.

### Outcomes

The following data are being systematically collected and analyzed throughout the trial.

#### Demographic and Baseline Data

Data on age, gender, race, height, weight, medical history, and medication history are being recorded for all participants.

#### General Physical Examination

Vital signs are being monitored and documented as part of the initial and follow-up assessments.

#### Safety Monitoring

Safety is being evaluated through a series of routine tests, including complete blood count, urinalysis, stool analysis, liver and kidney function panels, and electrocardiograms.

### Primary Efficacy Outcome

This study assesses the recurrence rate of perianal abscess as the primary endpoint, evaluated at 6 months (±7 d) after surgery. Recurrence is defined by the reappearance of clinical symptoms (eg, perianal pain, swelling, or purulent discharge) along with confirmation on a follow-up MRI scan—specifically the DTI sequence—of a new or persistent fluid collection suggestive of an abscess. For the purpose of this primary outcome, the presence of a newly developed anal fistula also constitutes a recurrence event. All assessments for recurrence are performed by 2 independent, experienced radiologists. These radiologists are blinded to the patient’s group allocation and baseline imaging findings. Any discrepancy between their assessments is resolved either by consensus or by a third senior radiologist.

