## Introduction

### Clinical Background and Diagnostic Challenges

Perianal abscesses are acute suppurative infections caused by obstruction of the anal gland opening and bacterial infection in the perianal tissues or spaces. They are among the most common anorectal diseases [1], particularly affecting young adults aged 20 to 40 years, with a higher prevalence in males than females [2]. Between 30% and 70% of patients with abscesses are often accompanied by anal fistula, while among patients without fistulas, the probability of developing an anal fistula is approximately 30% to 50% within months to years after abscess drainage [3]. Reducing recurrence rate and fistula rate of perianal abscesses remains a significant challenge. The recurrence rate after surgical intervention remains substantial, underscoring the need for improved diagnostic and therapeutic strategies [4].

The initial diagnosis of perianal abscesses is often based on clinical symptoms and anal palpation. However, this approach has limitations in dealing with multiple, high-grade perianal abscesses. In such cases, preoperative imaging, particularly magnetic resonance imaging (MRI), plays a pivotal role in accurate diagnosis and treatment [5,6]. MRI has a sensitivity of 96% and specificity of 97% for diagnosing abscesses [7]. Accurate assessment of the location, range, and depth of the abscess using MRI can help health care professionals develop more reasonable and effective surgical plans, including selecting the appropriate incision location, accurately positioning the internal opening, and employing the correct drainage method. This comprehensive approach aims to remove the infection as thoroughly as possible, reduce the risk of recurrence and fistula rate, and protect the anal function and quality of life of patients [8].

Diffusion-weighted imaging (DWI) is a variant of conventional MRI based on different rates of water diffusion in different tissues, offering unparalleled sensitivity to water motion within tissue structures [9,10]. Some studies have demonstrated the valuable role of DWI in the diagnosis and differential diagnosis of anal fistula and perianal abscess [11-13]. DWI exhibits high specificity in distinguishing abscesses from inflammatory masses, surpassing traditional MRI [12].

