Diffusion tensor imaging (DTI) extends the principles of DWI by modeling water diffusion as a 3D tensor, thereby quantifying both the magnitude and directionality (anisotropy) of diffusion within tissues [14]. Originally developed for neural tractography, DTI has shown promise in musculoskeletal and pelvic floor imaging by revealing microstructural integrity and architectural disruption [15]. A pivotal study by Wang et al [16] demonstrated the feasibility of DTI in evaluating perianal fistula, suggesting that parameters such as fractional anisotropy (FA) and apparent diffusion coefficient could reflect tissue characteristics relevant to surgical planning. However, while this and other emerging studies hint at DTI’s potential, the existing literature remains strikingly sparse regarding its specific application to perianal abscesses. Current evidence is largely extrapolated from fistula research or limited to technical feasibility reports. Critical gaps persist: there is a lack of standardized, quantitative DTI protocols for preoperatively mapping abscess extent, infection infiltration, and precise involvement of the anal sphincter complex and levator ani muscle. Moreover, it remains unclear whether the microstructural metrics provided by DTI correlate with surgical outcomes, such as recurrence rates or postoperative anal function.

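### The primary endpoint may miss or misclassify recurrences: it is confirmed on the test under evaluation, scheduled only at month 6, and has readers blinded to baseline imaging identify new fistulas

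*Protocol article*

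**What the plan says.** The protocol article's Primary Efficacy Outcome section gives two routes to a recurrence. In the first, symptoms return "along with confirmation on a follow-up MRI scan—specifically the DTI sequence", which must show a new or persistent collection. In the second, "the presence of a newly developed anal fistula also constitutes a recurrence event". The outcome is "evaluated at 6 months (±7 d) after surgery". Two radiologists make all recurrence assessments, blinded to "group allocation and baseline imaging findings".

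Other sections bear on this:

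- **Treatment Plan** gives the randomized contrast: "the control group receives conventional DWI, whereas the intervention group undergoes DTI".
- **Clinical Background and Diagnostic Challenges** says "MRI has a sensitivity of 96% and specificity of 97% for diagnosing abscesses" and gives no accuracy figure for DTI. It says that "there is a lack of standardized, quantitative DTI protocols" for mapping abscess extent before surgery. It also says: "Between 30% and 70% of patients with abscesses are often accompanied by anal fistula".
- **Table 1** marks recurrence only at t5 (6 months) and marks the DTI and MRI scans only before the operation.
- **Follow-Up Plan** lists contacts at days 3 and 7 and at month 6. Patients who cannot attend at month 6 are offered a telephone interview, with DTI if recurrence is then suspected.

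**The concern.** **(a) Index test as outcome test.** The sequence that distinguishes the arms also decides whether a symptomatic collection counts. As worded, a collection seen on T2 or post-contrast images but not on DTI is not an event. In the DTI arm, a lesion left behind because DTI did not show it could go unconfirmed for the same reason at month 6. Blinding the readers to allocation does not remove this, because the dependence lies in the test and not in the reader.

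**(b) Timing.** No contact is scheduled between day 7 and month 6, and no rule says how an event in that interval counts. A patient whose abscess recurred, was drained elsewhere and had healed by month 6 has neither symptoms nor a positive study scan. That patient would be recorded as recurrence-free rather than missing, so the multiple imputation in the Statistical Plan would not touch the case.

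**(c) New fistula.** Collections count whether new or persistent, so the reader needs no baseline for them. Fistulas count only if new, and newness cannot be judged from a month-6 scan alone.

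At stake is a primary comparison resting on so few events that a handful lost or misassigned could change the result.

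**Working it through.** **Inputs from the documents.** Recurrence 15% (conventional MRI) and 5% (DTI), 45 per arm, 41 evaluable after attrition (Sample Size Calculation). Accompanying fistula 30% to 70% (Clinical Background). The documents give no detection rate for DTI, no share of recurrences resolved before month 6 and no rate of old fistulas called new. These are assumed below, with ranges.

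**Expected events.** 45 × 0.15 + 45 × 0.05 = 6.75 + 2.25 = 9. With 41 evaluable per arm, 41 × 0.20 = 8.2.

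**The plan's own sample size.** The pooled two-sided formula at 15% versus 5% is n = [1.96√(2 × 0.10 × 0.90) + 0.842√(0.15 × 0.85 + 0.05 × 0.95)]² / 0.10², which gives 141 per arm. The stated 41 is not reproduced, and power at 41 is about 32%. That is a separate matter; 32% serves here only as the reference for the losses below.

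**(a) DTI confirmation.** Observed rate = true rate × detection probability.

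- *Equal detection in both arms, 90% down to 50%.* Observed rates run from 13.5% vs 4.5% to 7.5% vs 2.5%. The risk ratio stays at 0.05/0.15 = 0.33, so neither arm is favoured. Power at 41 per arm falls from 32% to between 29% and 18%.
- *Unequal detection, no true effect (15% in both arms).* Take 90% detection in controls and 80% down to 50% in the DTI arm. Controls read 0.15 × 0.90 = 13.5%; the DTI arm reads 12.0% down to 7.5%. The spurious difference is 1.5 to 6.0 points. The odds ratio runs from (0.120/0.880)/(0.135/0.865) = 0.87 to (0.075/0.925)/(0.135/0.865) = 0.52.
- *Control detection held at 100%.* With 10% to 40% of DTI-arm events missed, the DTI arm reads 13.5% to 9.0% against 15%. This is an upper bound for those inputs. In general the difference is 0.15 × (control detection − DTI-arm detection), so any miss in controls shrinks it.

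**(b) Events resolved before month 6.** If 30% to 50% of recurrences are treated and resolved in the gap, 9 × 0.70 = 6.3 down to 9 × 0.50 = 4.5 events remain. With the same share lost in each arm, the risk ratio again stays at 0.33 and the cost is information.

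**(c) Old fistula called new.** Let a fraction f of patients without a true event be counted, equally in both arms. The observed rate is p + (1 − p)f.

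| f | Control | DTI | Odds ratio | Power at 41 per arm |
|---|---|---|---|---|
| 0 | 15.0% | 5.0% | 0.30 | 32% |
| 5% | 19.3% | 9.8% | 0.45 | 23% |
| 20% | 32.0% | 24.0% | 0.67 | 12% |

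The odds ratio moves towards 1. The opposite error, a new fistula taken for an old one, loses events as in (b).

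**The case against.** The strongest reply is that the same DTI confirmation, with the same allocation-blinded readers, applies to both arms. This largely stands: equal under-detection leaves the risk ratio unchanged. A reader might infer that DTI confirmation does favour the DTI arm, by some 1.5 to 6 points. The documents do not support that. It needs correlated misses, for which they give no figure, and that size holds control-arm detection at 100%. Several facts also weaken the correlation:

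- Controls receive DWI, from which DTI is derived, so misses could correlate in that arm too.
- Both arms also have T1, T2, fat-suppressed and contrast sequences, and the surgical approach draws on symptoms and examination as well. A lesion not shown on DTI may still be found.
- The lack of standardized protocols concerns mapping extent before surgery. It does not say that DTI fails to detect a collection, and the 96%/97% quoted for MRI has no DTI counterpart.
- The DTI requirement attaches to the collection. A new fistula is a separate route to an event.

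On timing, the text nowhere says that recurrence counts only at month 6; this is inferred from the endpoint wording, Table 1 and the follow-up schedule. A 6-month recurrence rate can be read as cumulative, and adverse-event recording might pick up an interim event. But no rule makes such an event a primary outcome, and one that has healed still fails the symptoms-plus-DTI test.

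On fistula, a reader might infer that 27 to 63 patients (90 × 0.30 to 90 × 0.70) would be unclassifiable. Those are fistulas expected at baseline, before a resection meant to deal fully with the primary lesion; fewer would remain at month 6. The article also does not say that history or operative findings are withheld from the readers. It does not say they are supplied either.

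**Conclusion.** The point holds as a risk of missed or misclassified recurrences and should be fixed. A demonstrated bias is not established.

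- **(a)** could favour the DTI arm if DTI misses the same lesions before surgery and at follow-up. The direction is conditional and the size cannot be estimated from the documents.
- **(b)** loses abscess recurrences that are treated and resolved between day 7 and month 6 without a new fistula at month 6. The loss is alike in both arms in expectation. It matters because only about 9 events are expected.
- **(c)** is expected to be non-differential and to dilute the effect. This assumes that randomization balances baseline fistula and that misreading does not differ by arm.

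All detection, loss and misreading rates used here are assumptions. What rests on the text alone is that the endpoint, followed as written, can drop or misassign events.

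**What to change.** 1. Define the event as any recurrence from surgery to month 6 (+7 d).
2. Confirm it in both arms on the same non-DTI anatomical MRI sequences, read blind, or by documented pus or fistula at drainage or re-operation. Keep DTI as supplementary.
3. At the month-6 visit or call, ask about interim drainage or re-operation, obtain the record and count documented events.
4. Either count any fistula present at month 6, as is already done for collections, or add baseline and operative fistula status after the blind read is locked.
5. Show the follow-up imaging at t5 in Table 1.

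**Cost.** This amends the primary endpoint, so under Management of Protocol Amendments it needs ethics approval and a registry update. It should be settled before anyone sees outcomes by arm. The month-6 scan must include anatomical sequences, and some interim events will rest on outside records. Counting any fistula changes what the endpoint measures, and the amendment should say so. Recruitment began in April 2025 and 37 of 90 patients were enrolled by January 2026, so the earliest may already be past month 6. Their interim events would have to be sought retrospectively from records or by call, and their scans may not be repeatable.
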